### Outcomes

#### Primary Outcomes (Safety Assessment)

The main safety parameter is the incidence of hypotension requiring clinical intervention (≤90/60 mmHg). The secondary safety outcomes are the occurrence of adverse events including (1) neurologic deterioration defined as an increase of four or more points in the NIHSS within 7 days without clear explanation; (2) death during the study period regardless of cause; (3) body temperature down to below 36°C; (4) severe arrhythmias, such as sick sinus syndrome, rapid atrial fibrillation, supraventricular tachycardia, etc., which may cause palpitations, chest tightness, dizziness and other clinical manifestations; (5) liver damage: alanine aminotransferase (ALT) and aspartate aminotransferase (AST) concentrations were doubled; (6) seizures: epilepsy occurs within 2 weeks of stroke; (7) extrapyramidal responses (tremor, rigidity, salivation, and bradykinesia).

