### Interventions

Participants in both groups will receive the standard management according to the guidelines for the treatment of ischemic stroke, including blood pressure control, treatment of hyperglycemia and hyperlipidemia, antiplatelet or anticoagulation, and neurotrophic treatment (21). The body temperature of both groups will be maintained at 36.0–37.3°C. The room temperature will be 20–25°C. In order to ensure the stability of administration speed and the stability of blood pressure, patients allocated to the C+P group will undergo intravenous infusion of chlorpromazine 50 mg and promethazine 50 mg at 5 mg/h. For the choice of drug dosage, we referred to the hibernation mixture (chlorpromazine 50 mg + promethazine 50 mg) (13). Based on clinical experiences, this dose is safe and effective. The same total dose of C+P (25 + 25 mg, twice a day) given to patients has been proven to be safe in our previous study. In addition, as compared to oral administration, the current protocol with continuous small dose injection at 5 mg/h *via* a micropump will maintain a stable blood concentration. The speed will be adjusted according to the patient's reaction. This administration will keep the patient in light sedation that can be awakened and allow for physical examination at any time. The control group will receive the same dosage of normal saline at 5 mg/h. During this period, vital signs (i.e., blood pressure, heart rate, body temperature, respiratory rate of the patients), changes in consciousness, and possible adverse drug reactions will be closely monitored. If the patients show a tendency to develop adverse reactions and complications, the trial shall be stopped immediately, and routine treatment shall be given.

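### Infusions slowed or stopped for a falling blood pressure are not counted in the main safety parameter or in any listed outcome, which can tilt the safety comparison towards no increase

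*Protocol article*

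**What the plan says.** All references are to the protocol article.

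- **Primary Outcomes (Safety Assessment).** One main parameter is named: "The main safety parameter is the incidence of hypotension requiring clinical intervention (≤90/60 mmHg"). Seven further safety events follow as secondary safety outcomes, among them "body temperature down to below 36°C".
- **Interventions.** On the pump rate: "The speed will be adjusted according to the patient's reaction". On stopping: "If the patients show a tendency to develop adverse reactions and complications, the trial shall be stopped immediately, and routine treatment shall be given". On temperature: "The body temperature of both groups will be maintained at 36.0–37.3°C". The same section gives stable blood pressure as one reason for infusing slowly.
- **Statistical Analyses and Discussion.** Phase 2 follows if adverse reactions are no more frequent on C+P than on control and 90-day prognosis does not differ. The Discussion restates the safety part as the absence of a significant difference in drug-related adverse events.
- **Estimation of Sample Size.** 15 patients per group, chosen from pilot-study rules of thumb. No hypotension rate is stated.

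Neither outcomes section lists infusion slowing, interruption, stopping or delivered dose.

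**The concern.** The care rules act before the event definition does. If staff respond to a falling pressure by slowing or ending the infusion while it is still above 90/60 mmHg, the patient is free of the main safety event. Yet this is a reaction to the drug that limited the dose, which a first intravenous safety study most needs to see.

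The effect is unlikely to be equal between arms. The rules apply to both, but slowing saline averts no drug effect, so the averted falls sit mainly in the C+P arm. An undercount in that arm moves the comparison towards no difference, and that is the result that leads to phase 2. The phase-2 planners would also not learn from the listed outcomes how often the infusion could be given as planned, although feasibility is a stated aim.

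**Working it through.** **1. The passages side by side**

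| Situation on C+P | Action under Interventions | Main safety parameter | Other listed outcome |
|---|---|---|---|
| Abrupt fall to 90/60 mmHg or lower, needing intervention | Stop, routine treatment | Counted | – |
| Falling pressure, still above 90/60, pump slowed | Rate adjusted | Not counted | None |
| Falling pressure, still above 90/60, pump stopped | Stop, routine treatment | Not counted | None |
| Reading at or below 90/60, pump only slowed or stopped | As above | Unclear: the text does not say whether this is a clinical intervention | None |

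The main parameter therefore undercounts; it does not miss everything.

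**2. Size under assumed rates**

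There is no planned rate or power to reproduce: the 15 per group rests on rules of thumb. What follows shows direction and scale only.

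Inputs from the article: n = 15 per arm; p<0.05 (sidedness not stated, two-sided assumed); Fisher's exact test among the tests named. Assumed: the true event rate π on C+P, the rate on saline, and the share *a* of events averted and uncounted.

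*Events needed.* With 0/15 on saline:

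- 4/15: two-sided p = 2 × C(15,4)/C(30,4) = 2 × 1365/27405 = 0.100
- 5/15: two-sided p = 2 × C(15,5)/C(30,5) = 2 × 3003/142506 = 0.042

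So five C+P events are needed against none. Against one saline event seven are needed (p = 0.035), and against two, nine (p = 0.021).

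*Chance of reaching it.* Counted rate p = π(1 − a). With no saline events, the chance is P(X ≥ 5) for X ~ Bin(15, p).

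For π = 40%:

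| Averted share *a* | Counted rate | P(X ≥ 5) |
|---|---|---|
| 0 | 40% | 0.783 |
| 1/4 | 30% | 0.485 |
| 1/2 | 20% | 0.164 |
| 3/4 | 10% | 0.013 |

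Range for other assumptions (a = 0, 1/4, 1/2, 3/4):

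- π = 30%, saline 0%: 48%, 23%, 6%, 0.4%
- π = 50%, saline 0%: 94%, 72%, 31%, 3%
- π = 40%, saline 5%, averted in the same share: 52%, 32%, 12%, 1%

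The pattern is the same throughout. The starting level depends heavily on the assumed rates.

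**The case against.** **Safety of the infusion as managed is a fair question.** Rate adjustment belongs to the regimen that phase 2 might carry forward, and a fall that never reached 90/60 mmHg is not a miscounted 90/60 event. This stands, and is why the primary need not be replaced. But safety as managed can be interpreted only if the management is reported beside it.

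**The go rule is wider than the main parameter.** It speaks of adverse reactions, and the safety list is introduced as non-exhaustive. A stopped infusion could enter the decision as an adverse reaction. This also stands: the text does not exclude it, so the bias is possible and not certain. Nor does the text ensure it.

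**The adjustment rule does not name blood pressure.** Correct; it names the patient's reaction, and light sedation is discussed next. The stopping rule, however, covers any adverse reaction, and pressure stability is a stated purpose of the slow infusion.

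**Counting discretionary actions brings its own bias.** Under Randomization and Blindness the treating physicians open the envelopes, and only patients and assessors are named as masked. Physicians who know the allocation could slow C+P more readily. This is a good reason to keep such actions out of the primary event.

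**The illustration is hypothetical, and the small sample explains much of the weakness.** Agreed. At a true 30% the chance is only 48% before anything is averted.

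Two stronger readings are not supported. A reader might infer that the temperature rule contradicts the temperature outcome or biases the primary. Temperature below 36°C is a secondary safety outcome, and a target whose breach is the event is coherent. A reader might also take the stopping sentence to end the whole study at the first reaction. It goes on to routine treatment, so it describes one patient's treatment.

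**Conclusion.** The concern holds in a limited form. The main safety parameter counts hypotension only at the stated threshold and with intervention, while the Interventions section allows action before that point. No listed outcome records the action. Pressure falls that limit the dose, expected mainly on C+P, can therefore go uncounted and push the comparison towards no increase.

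The size cannot be determined from the article. Under the assumed 40% on C+P and 0% on saline, the chance of a significant difference falls from 78% to 48%, 16% or 1% as a quarter, half or three quarters of events are averted uncounted. This rests on the assumed rates, on all averted events going uncounted, and on a two-sided Fisher test.

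It would go too far to say that the primary outcome is invalid, that it misses hypothermia, or that the go decision rests on the 90/60 event alone.

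**What to change.** Leave the care rules and the primary threshold unchanged, and change what is listed and reported:

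1. Add a key safety outcome, compared by arm: any slowing, interruption or stopping of the study infusion with its reason (falling blood pressure shown separately), any treatment for falling pressure, and delivered dose.
2. Report all readings at or below 90/60 mmHg by arm, whether or not treated.
3. State that the go decision considers this outcome together with the primary.
4. Report active warming by arm beside the secondary outcome of temperature below 36°C.
5. Reconcile Interventions with Primary Outcomes on whether slowing or stopping the infusion counts as a clinical intervention. The sponsor must decide which is meant.

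The cost is outcome wording, a few entries on the infusion and care records, and the approvals that a change to a registered, ethics-approved trial requires. The added outcome is partly discretionary and may be decided by physicians who know the allocation, so it should be read beside the threshold-based primary and not replace it. The safety picture may look less favourable.

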
## Methods

### Study Design

This is a single-center, prospective randomized controlled trial. It will be performed in patients with acute ischemic stroke (AIS) onset within 24 h. Participants meeting inclusion criteria but not exclusion criteria will be randomly allocated to the C+P or the control group whether they received IVT or not. Participants allocated to the intervention group will receive intravenous administration of C+P within 24 h of symptom onset, within the first 60 min of administration. C+P will be administered after rt-PA if the patients received IVT. Seeing that early mechanical thrombectomy has an absolute difference in the rate of functional independence, as compared with alteplase alone (19, 20), this study will not include patients treated with EVT. *Via* the medical records, the demographic information, chronic medical history (diabetes, hypertension, hyperlipidemia, coronary heart disease), smoking history, alcohol drinking history, and NIHSS score at admission will be collected. Magnetic resonance imaging (MRI) will be performed at baseline and on days 3 and 90. NIHSS and mRS will be evaluated at baseline and immediately after administration, and on days 2, 3, 7, 14, and 90. All participants or proxies will be informed of potential risks and possible benefits and consented for this study. The consent will be provided to a legal representative if the patients do not have the capacity to consent. This study was approved by the ethics committee of Luhe Hospital, Capital Medical University, Beijing, China and has been registered at www.chictr.org.cn with ChiCTR2000038727. An independent physician will monitor the health and safety of the participants.

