## Discussion

A previous clinical study found that “lytic cocktail” [chlorpromazine 50 mg + promethazine 50 mg + dolantin (pethidine) 100 mg] reduced the mortality and neurological deficit of patients with acute cerebral hemorrhage and subarachnoid hemorrhage (13). Pethidine is mainly used for traumatic pain with acute cerebral hemorrhage and subarachnoid hemorrhage. Patients with acute ischemic stroke usually do not need analgesia, so in this study, we focused on the neuroprotective effect of C+P, without pethidine. Although a neuroprotective role was not investigated in acute ischemic stroke, our clinical study has demonstrated that the orally taken C+P at a dose of 12.5 + 12.5 mg or 25 + 25 mg, twice a day after AIS was safe by determining no serious adverse effects such as extrapyramidal symptoms, hypotension, seizures, abnormal liver function, ECG abnormality, and allergic reaction as well as NIHSS score and mRS in the treatment group compared with control group (14). Considering the low bioavailability of oral drugs, unstable blood drug concentration and other factors, the purpose of the present study will be to determine the safety, feasibility, and preliminary efficacy of the RICHES protocol. C+P will be intravenously administered, in order to establish a novel effective neuroprotective strategy. Our studies in rat ischemic stroke models demonstrated a neuroprotective effect of C+P. This protection was due to the reduction in the reactive oxygen species (ROS)-mediated oxidative injury (15), reduction in brain inflammation determined by the expression of TNF-α, IL-1 β, ICAM-1, VCAM-1, NF-κB (16), and reduction in apoptotic signal cascade (17), as well as improved integrity of blood-brain barrier (18). Importantly, the neuroprotection was induced in both hypothermic or normothermic conditions after ischemic stroke. In order to develop a translational strategy of neuroprotection, we will perform this study utilizing an intravenous infusion of C+P as a possible stable and effective therapy for AIS patients.

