With an aging population, the incidence of stroke will increase significantly (1, 25, 26). Good prognosis of AIS patients depends on timely revascularization and effective neuroprotective agents. At present, the effective methods of revascularization are thrombolysis and thrombectomy. However, the clinical efficacy of these therapies is limited by the narrow time window, potential complications and reperfusion injuries such as hemorrhagic transformation and brain edema (3, 27–29). Exploring fast and effective neuroprotective strategies to earn time for vascular recanalization and reduce reperfusion injuries has become an essential desire in AIS treatment.

Over the past few decades, there have been over 1,000 neuroprotective methods that have been examined for potential neuroprotective properties, mild hypothermia is the only one proven effective in randomized controlled trials. Although not included in the guidelines, the National Institutes of Health (NIH) points out that mild hypothermia is the most promising neuroprotective method for ischemic stroke. However, hypothermia is difficult to establish, slow in cooling and can easily lead to serious complications such as arrhythmia and pulmonary infection. This makes it difficult to achieve the clinical translation of benefits (21, 30, 31). During hibernation, the cerebral blood flow is decreased by <10%, but the utilization of glucose in the brain decreases by 98%, uncoupling metabolic demands (32). Therefore, an induced hibernation-like state might be a potential therapy for ischemic stroke by maintaining the body's low metabolism and low oxygen consumption even without low body temperature. This state may help the body survive prolonged hypoxia during the “difficult period of AIS.”

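### The named deterioration outcome counts only unexplained worsening, and intracranial haemorrhage is not a named safety outcome although rt-PA patients are enrolled

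*Protocol article*

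**What the plan says.** Under Primary Outcomes (Safety Assessment), the main safety parameter is hypotension needing intervention. The seven secondary items open with "The secondary safety outcomes are the occurrence of adverse events including (1) neurologic deterioration". To be counted under this first item, a patient must show "an increase of four or more points in the NIHSS within 7 days without clear explanation". The second is "death during the study period regardless of cause". The other five are low body temperature, severe arrhythmia, liver enzyme elevation, seizures and extrapyramidal responses.

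Four other places bear on this list:
- Study Design admits thrombolysed patients: "C+P will be administered after rt-PA if the patients received IVT".
- Interventions describes the intended effect: "This administration will keep the patient in light sedation that can be awakened and allow for physical examination at any time". It also requires monitoring of vital signs, consciousness and possible adverse drug reactions during the infusion.
- The Discussion mentions "reperfusion injuries such as hemorrhagic transformation and brain edema" among the limits of thrombolysis and thrombectomy.
- The Discussion says the group's oral C+P study looked at "extrapyramidal symptoms, hypotension, seizures, abnormal liver function, ECG abnormality, and allergic reaction".

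Statistical Analyses compares adverse-event frequency between arms. It makes a phase-2 trial conditional on no increase in adverse reactions and no difference in 90-day prognosis. The closing Discussion gives a second condition: no significant difference in adverse events related to the drug.

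**The concern.** In a safety trial, deterioration is normally counted first and explained afterwards. Here the explanation acts as a filter on counting. Two explanations that matter most in this trial are a bleed in a patient given rt-PA and over-sedation by the study infusion. Both are clear explanations, so both can remove a patient from the deterioration outcome. No other named item takes up a non-fatal bleed or over-sedation.

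The filter need not act equally on the two arms. Sedation from C+P can explain worsening only in patients who received C+P, so that exclusion would fall on the treated arm alone. The named row could then look balanced because events caused by the study drug had been taken out of it. The pilot's data feed the decision on a phase-2 trial, so what is defined and recorded now matters more than any single p-value.

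**Working it through.** The plan has no figure to reproduce on this point. The sample size of 15 per group comes from rules of thumb for pilot studies, without an event rate or power. The check is therefore mainly a reading of the passages against two cases.

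**Case A: non-fatal intracranial haemorrhage after rt-PA, NIHSS up by four or more within 7 days.**
- Main parameter (hypotension): not met by the bleed.
- Item 1 (deterioration): the bleed is a clear explanation, so the case can be excluded.
- Item 2 (death): not met.
- Items 3 to 7: none describes a bleed.
- General adverse-event comparison (Statistical Analyses): may count it.
- Go rule in Statistical Analyses (adverse reactions): depends on attribution. The 90-day prognosis condition reflects the bleed only through its lasting effect.
- Go rule in the Discussion (drug-related events): can miss it if it is attributed to rt-PA.

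**Case B: NIHSS up by four or more because the patient is over-sedated.**
- Item 1: sedation is the explanation, so the case can be excluded.
- Items 2 to 7: none describes over-sedation.
- General comparison and both go rules: may count it as an adverse reaction, but nothing defines when intended light sedation becomes an event.

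**Harms examined in the oral study against the present list.** Six harms are given for that study. Four have a counterpart here: extrapyramidal symptoms, hypotension, seizures and abnormal liver function. ECG abnormality is partly covered by severe arrhythmia. Allergic reaction has none.

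**Size at 15 per arm.** Event numbers and rates below are assumed; the document gives none.
- Suppose 3 of 15 C+P and 0 of 15 control patients worsen by four or more points, and all three cases are explained. The true split is 20% v 0%; item 1 shows 0/15 v 0/15.
- The one-sided 95% upper limit for 0/15 is 1 − 0.05^(1/15) = 18.1%, which is below the 20% that actually worsened.
- Two-sided Fisher p for x v 0 is 2·C(15,x)/C(30,x):
  - x = 3: 2 × 455/4,060 = 0.224
  - x = 4: 2 × 1,365/27,405 = 0.100
  - x = 5: 2 × 3,003/142,506 = 0.042
- The chance of at least one case among 15 treated patients is 1 − (1 − p)^15: 26%, 54%, 79% and 96% for true rates of 2%, 5%, 10% and 20%.
- Exact Fisher power in the harmful direction, by enumeration, is 8% for 20% v 5% and 52% for 40% v 5%.

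Naming the events would therefore rarely change a significance test. It would secure their definition and recording.

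**The case against.** The strongest reply is that the list is open. Its wording introduces the seven items as examples of adverse events. Statistical Analyses compares adverse events at large, and neither go rule is confined to the seven. Consciousness, respiratory rate and possible drug reactions are monitored. This is also a condensed article, and full recording rules may sit in a protocol that is not shown. All of that stands, and it keeps the point minor. It does not answer the deterioration definition, which is stated here and excludes explained worsening. Nor does it settle attribution, because the two go rules use different terms and one is limited to drug-related events.

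A reader might go further, but the document does not support these inferences:
- *That a bleed is counted only if fatal.* The open list can still record it, and its effect can show in the later NIHSS and mRS assessments.
- *That the arrhythmia item requires symptoms or leaves out ventricular arrhythmia.* The rhythms are given as examples, and the symptoms are described as possible consequences, not as a condition.
- *That the document itself names respiratory depression, aspiration pneumonia or QT change as C+P harms.* It does not. It also attributes haemorrhagic transformation to reperfusion, not to C+P.
- *That broad ECG outcomes could be added at no cost.* No ECG schedule is shown.

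Patients allergic to phenothiazines are excluded, which lowers the expected number of allergic reactions. It can act only on allergies already known.

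**Conclusion.** The point holds in a narrow form and is minor. The deterioration outcome drops worsening that has a clear explanation, and no named safety outcome captures intracranial haemorrhage or over-sedation. A bleed attributed to rt-PA can also fall outside the Discussion's go rule. Such events may still be recorded under the general comparison, so they are not assured of entering the safety assessment, rather than certain to be missed. Allergic reaction, examined in the oral study, has no named counterpart.

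No figure in the plan changes. The conclusion assumes that a scan-proven bleed or evident sedation would be accepted as a clear explanation, which is the ordinary reading of the clause.

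**What to change.** In Primary Outcomes (Safety Assessment):
1. Count every NIHSS rise of four or more points within 7 days, in both arms. Have the blinded observers record the cause separately.
2. Name any and symptomatic intracranial haemorrhage as a secondary safety outcome whatever the attribution. Read it on the day-3 MRI already scheduled or on any clinical scan, and report it by IVT status.
3. Name over-sedation, with a definition that separates it from the intended light sedation, using the consciousness monitoring already planned.
4. Name allergic reaction.

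In Statistical Analyses and the closing Discussion, use one term for the events that feed the go decision, and say whether attribution matters.

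The cost is wording in the protocol and case report form, plus a haemorrhage reading on MRI that the article describes only for infarct volume. Its sequence list names neither susceptibility-weighted nor gradient-echo imaging, so the reading method should be stated. The added rows will be sparse and are best reported as counts with exact confidence intervals.
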